#### Dance movement intervention

2.3.2

Participants in the Combined Intervention and DMI Only groups will participate in a structured Chinese Square Dancing program. Sessions will be held 3 times per week for 12 weeks, with each session lasting 60 minutes. The intervention emphasizes rhythm, coordination, memory of sequences, and social interaction. Participants in this group will receive in total thirty-six hours of intervention. A maximum of 10 participants will be enrolled in each DMI class to ensure performance quality. Instructors will use oral explanations and encouragements during the interventions.

Chinese square dancing movement programs have been applied within various populations showing evidence of benefits (Bisbe et al., 2020; Blumen et al., 2022; Zhu et al., 2018, 2022). Any 4 × 4 beats music can be used for dance intervention routine; participants will also be allowed to recommend music. The DMI will combine choreography and improvisation, single and partner strategies, including gentle body movements (consisting of limbs and spine movements) with special emphasis on rhythm and contralateral movement on both sides of the body to enhance coordination and stimulation between right and left cerebral hemispheres (Ho et al., 2015, 2020). The DMI routine contains repetition and improvisation; therefore, it will require memory, concentration and dual-task function to complete the dance correctly.

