The dance moves are gender-neutral and applicable to both males and females. Dance routines will be adapted to participants’ abilities, and new routines may be introduced every three to four weeks. Each session will be led by one dance instructor positioned at the front of the group, who will lead the dance and encourage social connection. A second instructor and supporting medical staff will supervise participants’ movements, guide correct execution, and ensure safety. The DMI targets both motor participation and specific cognitive processes. At the motor level, the choreographed and improvised routines are designed to engage whole-body coordination, balance, and cardiovascular demand. At the cognitive level, the routines are designed to engage attention, working memory, motor planning, and executive function—through memorizing step sequences, synchronizing movements to music, adapting to changing choreographic patterns, and engaging in partner-based interactions. Participants are not required to perform movements with 100% accuracy; rather, the emphasis is on sustained engagement with both the motor and cognitive demands of the task, in order to experience the body as a source of creativity and reliability. A practice video featuring standard movements will be provided after each class to support at-home familiarization. Rest periods, during which participants may sit and drink water, are built into each session. To accommodate older participants, the dance intervention can be performed in seated positions when needed to reduce fatigue. Intervention fidelity and adequate involvement will be documented session-by-session using a structured adherence log completed by the supervising instructor. The log will capture: (i) session attendance and duration of active participation; (ii) instructor-rated movement engagement and quality on a 5-point Likert scale; (iii) proportion of the session completed in standing versus seated position; and (iv) any adverse events or safety concerns. These data will be used to characterize intervention delivery and to support per-protocol analyses.

Each dance class will consist of six structured components, delivered in the following sequence:

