Warm-up (10 min) — stepping combined with breathing, head movement, spinal side-bending, and turning exercises.DMI choreography (30 min) — three structured routines performed in unison to music; the third routine includes interactive movements with partners.Break (5 min) — seated rest and water intake.DMI improvisation (15 min) — the instructor performs movements at the front of the group; participants may follow along, dance independently, or engage in interactive movements with partners.Cool-down (5 min) — slow stretching and breathing, combined with low-speed stepping.Social sharing (10 min) — facilitated group discussion in which each participant is invited to use one or two words, a gesture, or a movement to express their feelings, enjoyment, and playfulness regarding the dance experience, and to share words of encouragement or care with one another.

These six steps aim to encourage the participants to remember steps and sequences; concentration and memory will be required to perform this dance routine smoothly and correctly; improve mood and vitality, foster imagination and creativity. In addition, attention and planning movement in space with the aim of using movement activities and paying attention to bodily experiences to improve cognitive function. Furthermore, personal expression (verbal and non-verbal) to enhance communication and social exchange, respectively. For treatment fidelity, before the intervention, two instructors will teach two classes as practice for dance intervention groups. Every class will last one hour, with a one-day gap between the two classes. In these sessions, researchers will explain the essentials of DMI—including the six-component class structure (warm-up, choreography, break, improvisation, cool-down, and social sharing), safety guidelines (footwear, hydration, permission to rest in a seated position at any time, and the principle that movements need not be 100% accurate), and use of the post-class practice video—together with its potential health benefits for older adults with MCI, including improvements in motor function (balance, coordination, cardiovascular fitness), cognitive function (attention, working memory, motor planning, executive function), social engagement, and emotional well-being. Participants will then be introduced to basic movements through guided practice with instructor feedback.

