A sign-in system will be implemented for each class during the investigation, and a small gift or daily necessities (towel, soap, toothbrush, etc.) will be awarded to those participants who attended intervention sessions. The aim of training monitoring is to check exercise interventions’ training intensity. The interventions will be conducted as moderate intensity, based on levels of perceived exertion. Participants will be instructed to carry out their intervention activities without exceeding 4–6 points on the Borg Scale (0 to 10 scale) (Borg, 1982). Instructors will regularly ask participants about their perceived fatigue levels during activities and help them to maintain the target level of effort.

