#### Social activity control

2.3.3

To control for the social interaction and general engagement inherent in the DMI, participants in the rTMS Only and Control groups will attend time-matched sessions (60 minutes, 3 times per week) involving non-aerobic activities such as watching educational videos, listening to music, and engaging in supervised, non-strenuous group discussions.

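### The dance groups get two extra practice hours and a cognitive-benefit briefing with no described counterpart in the time-matched social control, so the DMI effect cannot be attributed to dancing alone

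*Protocol article*

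**What the plan says.** The protocol article describes the dance programme in section 2.3.2 and the social control in section 2.3.3.

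**Dance arms (Combined and DMI Only).** "Sessions will be held 3 times per week for 12 weeks, with each session lasting 60 minutes", and "Participants in this group will receive in total thirty-six hours of intervention". Three further elements follow:

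- **Practice classes.** "before the intervention, two instructors will teach two classes as practice for dance intervention groups". Each lasts one hour. Researchers use them to explain the class structure and the safety rules, and also what dancing may do for people with MCI. Executive function and working memory are among the gains named.
- **Home video.** "A practice video featuring standard movements will be provided after each class", for use at home.
- **Sign-in and gifts.** A sign-in system runs for each class, and a small gift "will be awarded to those participants who attended intervention sessions". The sentence stands in the dance section but names no arm.

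**Social arms (rTMS Only and Control).** Section 2.3.3 provides "time-matched sessions (60 minutes, 3 times per week) involving non-aerobic activities" and says that they control for the social and engagement side of the dance programme. It describes no orientation, briefing, take-home material, sign-in or gift.

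**Related text.** Section 2.8 says that participants cannot be blinded. Section 3.7.2 says that everyone is told at consent about both interventions and what benefit may be expected. Section 2.9.1.3 tests the two main effects and their interaction on the primary outcome.

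**The concern.** A time-matched attention control exists so that a difference between dance and social arms can be credited to the dancing, and not to being seen more often or expecting to do better. Section 2.3.2 loosens that match in a way that section 2.3.3 does not acknowledge.

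The briefing matters more than the two hours. It tells participants, who know that they are in a dance arm, that dancing may improve the abilities on which they will be tested. By the protocol's own description (section 2.4.1) the MoCA covers executive function, memory and attention, and section 2.10 makes the TMT-B/A ratio a key secondary outcome. Assessor blinding protects the scoring; it does not remove a participant's expectation or effort on a performance test. The formal blinding check in section 2.6.2 computes Bang's index for active and sham iTBS, so it would not show expectancy attached to dance.

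Attendance gifts are a separate question. Section 2.2 lists missing more than six sessions, without making them up, as a ground for stopping. An incentive offered in some arms and not others could therefore affect retention. Whether it is so offered cannot be told from the text.

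**Working it through.** **1. Contact hours.** Inputs are from sections 2.3.2 and 2.3.3.

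- Plan's own figure: 3 sessions/week × 12 weeks × 1 h = 36 h. This reproduces the stated total.
- Social control at the same frequency and length over 12 weeks: 36 h.
- Dance with the practice classes: 36 + 2 × 1 = 38 h.
- Excess: 38/36 − 1 = 5.6%.

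Home video time is not counted, because no expected duration is given and no log item records it.

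The six listed class components sum to 10 + 30 + 5 + 15 + 5 + 10 = 75 minutes, while the stated session length is 60. Taken at face value the list would give 36 × 75/60 = 45 h, or 47 h with practice, against 36 h (+30.6%). I do not rely on that figure. The two passages must be reconciled, since the claim of time-matching depends on them.

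**2. Which contrasts are affected.** Let the extras add a non-specific amount b to the outcome in both dance arms and nothing in the social arms, so that Combined = b, DMI Only = b, rTMS Only = 0 and Control = 0.

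| Contrast | Formula | Shift |
|---|---|---|
| DMI main effect | [(b + b) − (0 + 0)]/2 | b |
| Combined v Control | b − 0 | b |
| Combined v rTMS Only | b − 0 | b |
| Combined v DMI Only | b − b | 0 |
| rTMS main effect | [(b + 0) − (b + 0)]/2 | 0 |
| rTMS × DMI interaction | b − 0 − b + 0 | 0 |

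The zeros hold only if b is the same with active and with sham stimulation.

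**3. What a given b would do (illustration only).** The document gives neither b nor an SD for MoCA change, so both are assumed: SD 2.5 to 3.5 points, b = 0.25 or 0.5 points. The planned 128 completers split into 64 dance and 64 social. SE = SD × √(2/64), which is 0.44 to 0.62 points. With no true dance effect, the chance of a significant DMI main effect at two-sided 0.05 is Φ(b/SE − 1.96) + Φ(−b/SE − 1.96):

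| b (points) | SD 2.5 | SD 3.0 | SD 3.5 |
|---|---|---|---|
| 0.25 | 8.7% | 7.6% | 6.9% |
| 0.5 | 20.5% | 15.6% | 12.8% |

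The nominal rate is 5%. The table shows how the test responds to an assumed bias; it does not estimate that bias.

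**The case against.** The strongest reply is that the practice classes and the video are part of the treatment. Section 2.3.2 introduces the classes for fidelity, they teach safety and basic steps, and the video shows dance movements. The control is set to match social contact and engagement, not dance instruction. This stands for the movement teaching and the video: they belong to the DMI package, and the remedy is to report the effect as that of the package. It does not cover the benefit briefing, which is not movement training.

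A second reply is that expectancy would exist anyway, since all arms hear about expected benefits at consent and everyone knows whether they dance. That also stands in part. The briefing is an additional dose given to the dance groups, not the only source.

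A third is that an article condenses the full protocol, so silence in section 2.3.3 proves little. That is fair for sign-in and gifts. It is weaker for the practice classes and briefing, which the text expressly assigns to the dance groups.

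Some stronger readings are tempting but unsupported:

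- **Gifts in the dance arms only.** Placement and the reference to classes lean that way, but no arm is named. Section 2.9.1 uses similar wording about sessions for the whole trial, and Table 1 lists the social activity under interventions.
- **Bias from differential dropout.** This needs unequal gifts, a dropout gap and a difference between dropouts and completers that the mixed model misses. None of these can be sourced from the document.
- **A log meant for all arms.** Section 2.3.2 says that the session log supports per-protocol analyses, but does not say across arms.
- **A compromised synergy test.** Under an additive effect the interaction does not shift.

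**Conclusion.** The concern holds in limited form. The dance groups are given two extra hours (38 v 36 h, +5.6%) and a briefing on possible cognitive gains. The social control, described as time-matched and as controlling for engagement, has no stated counterpart. Whether sign-in and gifts reach the social arms is ambiguous.

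Any non-specific effect of extra contact and primed expectation passes in full into the DMI main effect, Combined v Control and Combined v rTMS Only. The rTMS main effect and the rTMS × DMI interaction are unaffected, provided that the effect is additive. The size of the bias cannot be derived from the document. What is established is a mismatch that limits attribution of these contrasts to dancing itself, not a demonstrated false result.

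**What to change.** 1. Remove the benefit claims from the dance practice classes, or use one neutral briefing script in all four arms.
2. Give the social arms an orientation of matched length.
3. State in sections 2.3.2 and 2.3.3 that sign-in, attendance gifts and a log of attendance and duration apply in every arm. The movement-quality and standing/seated items stay with the dance arms, since they have no meaning for the social sessions.
4. Describe the practice video and movement familiarisation as part of the DMI package, log video use, and report the DMI effect as that of the package.
5. Reconcile the stated session length with the component list, so that the claim of time-matching can be checked.

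The cost is small gifts for about 80 more participants (2 × 40, if they are not already covered), two short group orientation sessions, a revised script and an added log field. Randomisation, sample size and endpoints do not change.

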#### Social activity control

2.3.3

To control for the social interaction and general engagement inherent in the DMI, participants in the rTMS Only and Control groups will attend time-matched sessions (60 minutes, 3 times per week) involving non-aerobic activities such as watching educational videos, listening to music, and engaging in supervised, non-strenuous group discussions.

### Measurement outcomes

2.4

Assessments will be conducted at three time points: Baseline (T0), Post-Intervention (T1, Week 12), and Follow-up (T2, Week 24). T1 assessments will be conducted 24–72 hours after the final intervention session of Week 12, to avoid the potential confounding influence of acute rTMS and dance exposure on cognitive and physical performance. To control for circadian variation, T1 and T2 assessments for each participant will be scheduled at the same time of day as that participant’s T0 assessment. Participants’ self-rated scales will be completed under guidance. All the tests will be administered in accordance with the standard procedures. The specific schedule of enrolment, interventions, and assessments is detailed in **Table 1**.

**Table 1 T1:** SPIRIT schedule of enrolment, interventions, and assessments.

Procedure	*Enrolment*	*Allocation*	*Intervention Phase*	*Post-Intervention*	*Follow-up*
*Timepoint*	-t_1_ (Screening)	T0 (Baseline)	Weeks 1–12	T1 (Week 12)	T2 (Week 24)
Enrolment:					
*Eligibility Screening*	**X**				
*Informed Consent*	**X**				
*Demographics & Medical History*	**X**				
*Inclusion MoCA, GDS-15, BBS*	**X**				
*Randomization*		**X**			
Interventions:					
*Active or Sham iTBS (rTMS)*			**X**		
*Chinese Square Dancing (DMI)*			**X**		
*Social Activity Control*			**X**		
Assessments:					
Primary outcome					
*Montreal Cognitive Assessment (MoCA)*		**X**		**X**	**X**
Secondary outcomes					
*Wechsler Memory Scale (WMS-IV)*		**X**		**X**	**X**
*Trail Making Test (Part A & B)*		**X**		**X**	**X**
*Berg Balance Scale (BBS)*		**X**		**X**	**X**
*6-Minute Walk Test (6MWT)*		**X**		**X**	**X**
*12-item Short Form Survey (SF-12)*		**X**		**X**	**X**
Neurophysiological & exploratory					
*EEG/ERP (P300 Oddball paradigm)*		**X**		**X**	
*Resting-State fMRI (rs-fMRI)*		**X**		**X**	
Safety & fidelity					
*Adverse Events Monitoring*			**X**	**X**	
*Blinding Integrity Questionnaire*				**X**	
*Qualitative Interviews*					**X**

-t₁: Initial screening phase to determine clinical eligibility based on MoCA, Geriatric Depression Scale (GDS-15), and Berg Balance Scale (BBS) inclusion criteria. T0: Baseline assessment conducted immediately prior to randomization. T1: Primary endpoint assessment conducted immediately following the 12-week intervention. T2: Follow-up assessment conducted 12 weeks post-intervention to determine durability of effects. MoCA, Montreal Cognitive Assessment; GDS-15, 15-item Geriatric Depression Scale; WMS-IV, Wechsler Memory Scale Fourth Edition; BBS, Berg Balance Scale; 6MWT, 6-Minute Walk Test; SF-12, 12-item Short Form Health Survey; EEG/ERP, Electroencephalography/Event-Related Potential; rs-fMRI, Resting-state Functional Magnetic Resonance Imaging.

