The study would cease if any of the following occurs: (1) Participant’s death. (2) Medical problems related to exercises (fracture, cardiac or cardiopulmonary problems, etc.). (3) Participants experience adverse event(s) that require discontinuation in the judgment of the principal investigator or trial instructor. (4) Participants have a need for additional intervention (such as cognitive treatment) that would interfere with the trial. (5) Participant neglects to follow trial instructions. (6) Participant have lost more than six sessions and cannot make additional lessons to cover the deficiency. (7) Participants or their legally authorized representative request consent withdrawal. An adverse event will be defined as any untoward medical occurrence in a participant during participation in the study. Adverse events include unbearable discomfort with rTMS intervention, falling, tripping, serious muscle soreness during dance participation. Participants will be allowed to finish all dance classes in a sitting position to prevent further adverse events if necessary.

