### Intervention protocol

2.3

The study consists of a 12-week intensive intervention phase followed by a 12-week follow-up phase. This 12-week duration is chosen based on evidence that significant cognitive and neuroplastic changes in MCI populations typically manifest within 3 months of rTMS and structured exercise (e.g., dance) (Guo et al., 2025; Sánchez-Alcalá et al., 2025). While a 24-week intervention was considered, the 12-week model is preferred to maximize participant retention and minimize “intervention fatigue” in this elderly population, while still being sufficient to demonstrate synergistic effects (Ren et al., 2025). The subsequent 12-week follow-up will allow for the assessment of the durability of these effects—a critical factor for clinical translation. Participants will be supervised by trained instructors and medical staff.

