### Sample size

2.7

A priori power analysis (G*Power 3.1) was conducted for a four-group repeated measures ANOVA (interaction effect). To detect a medium effect size (f = 0.25) with a power of 0.8 and an alpha level of 0.05, a total sample of approximately 128 participants (32 per group) is required. To account for potential participant dropouts, we have factored in an anticipated attrition rate of 20% over the 24-week study period (12-week intervention plus 12-week follow-up). This 20% estimate is intentionally conservative and rigorously justified by previous longitudinal literature involving older adults with cognitive impairment. Systematic reviews of intensive, multi-modal non-pharmacological interventions (including aerobic exercise and neuromodulation protocols) in geriatric populations consistently report attrition rates ranging from 15% to 21%, typically due to transportation barriers, intervention fatigue, or unrelated emergent health issues (Di Lorito et al., 2020). Therefore, to ensure the trial remains adequately powered throughout the follow-up phase, we aim to recruit a final total of 160 participants (40 per group).

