#### Safety monitoring and serious adverse event reporting protocol

3.7.5

An Adverse Event (AE) is defined as any untoward medical occurrence in a participant during the study, regardless of its causal relationship with the intervention. Expected, mild AEs (e.g., transient scalp discomfort from iTBS, mild delayed-onset muscle soreness from the DMI) will be managed conservatively by the supervising medical staff and documented in the participant’s case report form (CRF).

A Serious Adverse Event (SAE) is strictly defined as any event that results in death, is life-threatening, requires inpatient hospitalization, or results in persistent or significant disability/incapacity. In the event of an SAE, a rapid-response reporting protocol will be initiated. The supervising trial instructor must notify the Principal Investigator immediately (within 24 hours of awareness). The Principal Investigator is then legally and ethically mandated to formally submit a detailed SAE report to the Medical Ethics Committee of Handan Central Hospital within 48 hours. Furthermore, the trial steering committee will evaluate the SAE to determine if trial protocols require modification or suspension, and the event will be officially updated and disclosed on the Chinese Clinical Trial Registry in accordance with international trial transparency guidelines.

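### Table 1 schedules adverse-event monitoring only to T1 (Week 12), while adverse events are defined over a 24-week study, so none are actively elicited during follow-up

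*Protocol article*

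**What the plan says.** **Schedule.** Table 1 in section 2.4 of the protocol article has a safety row, "Adverse Events Monitoring". It is marked in the column for Weeks 1–12 and in the T1 column. The T2 (Week 24) cell is empty. On T1 itself, section 2.4 says: "T1 assessments will be conducted 24–72 hours after the final intervention session of Week 12".

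**Definition.** Two sections define an adverse event, and neither ends the definition at Week 12. Section 2.2 has "any untoward medical occurrence in a participant during participation in the study". Section 3.7.5 has "any untoward medical occurrence in a participant during the study, regardless of its causal relationship with the intervention".

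**Length of the study.** Section 2.3: "The study consists of a 12-week intensive intervention phase followed by a 12-week follow-up phase". Section 2.7 gives the same total of 24 weeks when it sets the attrition allowance.

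**Other recording routes.** In section 2.3.2 the instructor's session log for the dance arms includes "any adverse events or safety concerns". In section 3.7.5, mild expected events are entered in the case report form by the medical staff who supervise. A serious event is passed by the supervising trial instructor to the principal investigator within 24 hours of awareness, and from there to the ethics committee within 48 hours.

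**The concern.** The definition of an adverse event covers everything that happens to a participant during the study, whether or not the intervention caused it. The schedule tells staff when to look, and it stops at T1. A site that follows Table 1 would not ask about events at Week 24, and an event in follow-up would enter the record only if someone happened to mention it.

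This matters in this trial for two reasons. Participants are aged 50 to 85 with MCI. Falls are a named adverse event, and hospital admission and death are serious ones; these can occur in any week. The trial also sets out to show that benefit lasts: section 2.3 gives durability as the purpose of the follow-up phase, and section 4 hypothesises more durable improvement in the combined arm. Benefit would be observed to Week 24, while harm would be sought only to about Week 12. The steering committee's review of serious events in section 3.7.5 likewise depends on events coming to notice.

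**Working it through.** **Step 1. Study length.** Inputs: 12 weeks of intervention and 12 weeks of follow-up (sections 2.3 and 2.7). 12 + 12 = 24 weeks, which reproduces the total in section 2.7.

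**Step 2. Is the blank cell real?** Table text taken from a PDF can shift by a column, so neighbouring rows were read in the same way:

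| Table 1 row | Columns marked |
|---|---|
| MoCA | T0, T1, T2 |
| Blinding questionnaire | T1 |
| Qualitative interviews | T2 |
| Adverse events | Weeks 1–12, T1 |

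The other rows fall where the text says they should: MoCA at all three assessments (section 2.9.1.2), the blinding questionnaire at T1 (section 2.6.2) and the interviews at Week 24 (section 2.5.2). The empty T2 cell is therefore not a column shift.

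**Step 3. Does another route cover Weeks 12–24?**

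- The dance log (section 2.3.2) is filled in session by session, and sessions end at Week 12. It also exists only for the two dance arms.
- The case report form entries for mild events (section 3.7.5) come from staff supervising the interventions, which also end at Week 12.
- The serious-event route (section 3.7.5) has no end date. It is triggered by awareness and starts with the trial instructor. The article describes no contact between instructors and participants after Week 12.

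No passage schedules elicitation of events after T1.

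**Step 4. Share of time without scheduled monitoring.**

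- Taking T1 as the end of Week 12: 12 / 24 = 0.50.
- Taking T1 at the latest point of its window, 72 hours (3/7 week) after the end of Week 12: (24 − 12 − 3/7) / 24 = 11.57 / 24 = 0.48.

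**Step 5. Participant-weeks.** Input: 160 randomised (section 2.7, where 128 / 0.80 = 160 reproduces the target).

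- Planned time: 160 × 24 = 3,840.
- Without scheduled monitoring: 160 × 12 = 1,920, which is 1,920 / 3,840 = 0.50.
- If the whole 20% attrition fell before follow-up: 160 × 0.80 = 128 followed, and 128 × 12 = 1,536 participant-weeks. The figure of 1,920 is therefore an upper bound.

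**Step 6. After the change.** If the row runs through follow-up and T2 is marked, no follow-up week lies outside scheduled collection for anyone who attends T2. Participants who miss T2 are not reached by this alone.

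**The case against.** The best case for the plan is that a definition and a collection period are different things. Sections 2.2 and 3.7.5 say what counts as an adverse event; neither mentions Week 24, and the 24-week reach comes from joining them to sections 2.3 and 2.7. No study intervention is given after Week 12, most of the examples of adverse events concern stimulation or dance, and T1 one to three days after the last session gives a short window for late effects. A team may choose to confine active monitoring to the treated period. The article also condenses a fuller protocol, and the case report form is not shown.

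Part of this stands. Stopping at the end of treatment would be a legitimate choice if the plan stated it. It does not: it counts events regardless of cause and sets no cut-off. Nor is this a detail left to another document, since Table 1 states when monitoring takes place and the definitions state something wider.

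Four stronger readings are tempting and are not supported.

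- *That follow-up has no safety collection at all.* The serious-event duty in section 3.7.5 has no end date, so a death or admission that staff learn of in Weeks 12–24 is still reportable. What is absent is scheduled elicitation.
- *That reasons for loss to follow-up would go unrecorded.* Recording these is a matter of participant flow, not of the adverse-event row. Section 2.2 lists discontinuation reasons, the Figure 2 caption carries participants to Week 24, and nothing says reasons are not kept.
- *That a promised safety reporting period would be missed.* The article states no such period, and the outcome hierarchy in section 2.10 contains no safety outcome.
- *That 1,920 participant-weeks measures lost events or bias.* It measures calendar time only. The documents give no event rates from which missed events could be estimated.

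**Conclusion.** The point holds as a mismatch between passages of the current text. Table 1 schedules adverse-event monitoring for about 12 weeks; the definitions, read with the stated study length, cover 24. As written, no adverse events are actively elicited in follow-up. This is 48% to 50% of planned time per participant, and at most 1,920 of 3,840 participant-weeks before dropout.

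The conclusion assumes that sites work from Table 1 as printed, and that words such as study and participation in the definitions carry the 24-week meaning the protocol gives the study elsewhere. Serious events remain reportable on awareness, though the first link in that chain has no stated contact with participants after Week 12.

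The consequence is an incomplete record of harm over the period in which durability of benefit is assessed. Power, type I error and the primary MoCA comparison at T1 are not affected.

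**What to change.** Reconcile Table 1 with sections 2.2 and 3.7.5:

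- Extend the adverse-event row of Table 1 through the follow-up phase and mark T2.
- At T2, ask the same standard adverse-event question in all four arms, covering the time since T1, and record onset dates so that events can be assigned to a period.
- Report events by arm, separately for the intervention and follow-up periods.
- State in section 3.7.5 who receives and passes on a serious event once sessions have ended.

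The cost is a table edit and a few minutes at a visit that participants already attend for six outcome measures. One limit remains: a single question with 12 weeks' recall, put to people with MCI, is likely to miss some minor events. It would still be more complete than no question, and it would be asked identically in every arm.
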